## Abstract

**Background:**

Hospitalisations are a critical event in the care process. Insufficient communication and uncoordinated follow-up care often impede the recovery process of the patient resulting in a high number of rehospitalisations and increased health care costs. The overall aim of this study is the development, implementation and evaluation of a structured programme (VESPEERA) to improve the admission and discharge process.

**Methods:**

We will conduct an open quasi-experimental multi-centre study with four intervention arms. A cohort selected from insurance claims data will serve as a control group reflecting usual care. The intervention will be implemented in 25 hospital departments and 115 general practices in 9 districts in Baden-Wurttemberg. Eligibility criteria for patients are: age > 18 years, hospital admission or hospitalisation, insurance at the sickness fund “AOK Baden-Wurttemberg”, enrolment in general practice-centred care contract. Each study arm will receive different intervention components based on the point of study enrolment and the patient’s medical need. The interventions comprise a) a structured assessment in the general practice prior to admission resulting in an admission letter b) a discharge conversation by phone between hospital and general practice, c) a structured assessment and care plan post-discharge and d) telephone monitoring for patients with a high risk of rehospitalisation. The assessments are supported by a software tool (“CareCockpit”), originally developed for structured case management programmes. The primary outcome (rehospitalisation due to the same indication within 90 days) and a range of secondary outcomes (rehospitalisation due to the same indication within 30 days; hospitalisations due to ambulatory care-sensitive conditions; delayed prescription of medication and medical products/ devices and referral to other health practitioner/s after discharge; utilisation of emergency or rescue services within 3 months; average care cost per year and patient participating in the VESPEERA programme) and quality indicators will be determined based on insurance claims data and CareCockpit data. Additionally, a patient survey on satisfaction with cross-sectoral care and health related quality of life will be conducted.

**Discussion:**

Based on the results, area-wide implementation in usual care is well sought. This study will contribute to an improvement of cross-sectoral care during the admission and discharge process.

**Trial registration:**

DRKS00014294 on DRKS / Universal Trial Number (UTN): U1111–1210-9657, Date of registration 12/06/2018.

## Background

Hospital discharges are a critical moment in healthcare delivery as continuity of care is crucial for patient safety. In daily practice, patients are often discharged at short notice, resulting in a lack of coordination of follow-up care and sufficient communication between care providers of the inpatient and outpatient sector and to the patient [1–3]. This can be due to different organisational procedures and different views on the patient and responsibilities with regard to the care process between hospitals and general practices [4] as well as between interprofessional teams [5]. The resulting interruptions in the continuity of care can affect the recovery process and healthcare related patient satisfaction. At worst, they can lead to avoidable rehospitalisations and adverse events [1, 4], which are relevant clinical outcomes and associated with increased care costs.

A project on harmonisation of admission and discharge medication showed the need for improvement of information brokerage concerning pre- and post- hospital medication as well as structured medication counseling after discharge [3].

Structured admission and discharge management are essential and inseparable components of optimal transitional care. Numerous systematic reviews provide overviews on evaluated transitional care programmes. For example, Leppin et al. found that a multicomponent intervention comprising many care providers with components such as case management, a telephone follow-up, patient-centred discharge information, and patient education significantly reduced readmission rates for medical and surgical patients [6]. In another review, Branowicki and colleagues implemented post-discharge interventions like follow-up phone calls, home visits, and discharge education [7]. The intervention showed that home visits and having two or more follow-up phone calls significantly reduced readmission rates. Vedel et al. conducted a review with studies focusing on transitional care interventions for patients with heart failure [8]. Intervention components included in the studies were telephone follow-up, individualised treatment plans, and medication schedules. The authors found that high intensity interventions significantly reduced readmission rates. Furthermore, they found a significant effect on reduction of emergency department visits. The results of Hansen et al. indicate that early discharge planning, follow-up phone calls and patient-centred discharge instructions may reduce 30-day rehospitalisation rates [9]. In another systematic review, Hesselink and colleagues gather studies that suggest structured discharge information, coordination of follow-up care and timely communication between care providers are components of successful discharge interventions [4]. Burke et al. found interventions in the domain “Systems for Monitoring and Managing Symptoms” of the Ideal Transitions Framework to be successful in reducing rehospitalisation rates [10]. Bahr et al. investigated post discharge telephone calls in single component interventions but could not find clear evidence on their effectiveness on reducing rehospitalisation rates and emergency department use and increasing patient satisfaction [11]. However, the authors suggest that further research should focus on telephone calls as a component of complex interventions involving outpatient care providers and high risk patients. In many systematic reviews, authors cannot draw firm conclusions, because the intervention components of the included studies are very heterogeneous and often lack comprehensible descriptions [4, 9, 12]. Nevertheless, some authors indicate that multicomponent interventions have a positive effect on outcomes such as rehospitalisation rates, emergency department visits, patient satisfaction, or health care cost [4, 9].

To date, in Germany there are few established standards for cross-sectoral communication related to arranged admission and discharge planning. Recent changes to German federal laws and regulations aim to improve transitions between care sectors. For example, the Act to Enhance Competition in Statutory Health Insurance (*Gesetz zur Stärkung des Wettbewerbs in der gesetzlichen Krankenversicherung*) aims to improve quality and efficiency of health care by enhancing competitions amongst care providers and sickness funds. A further example is the Act to Act to Promote Health Care in Statutory Health Insurance (*Gesetz zur Stärkung der Versorgung in der gesetzlichen Krankenversicherung*), which aims to improve continuity of patient’s care when discharged from hospital to other care providers. Still, fragmentation in care remains a complex challenge. With effect as of October 1st 2017, hospitals in Germany are obligated to offer a structured discharge planning to all patients according to the framework contract regarding hospital discharge management (“*Rahmenvertrag über ein Entlassmanagement beim Übergang in die Versorgung nach Krankenhausbehandlung nach § 39 Abs. 1a S.9 Sozialgesetzbuch V*”). However, this framework contract does not demand to conduct pre-hospital interventions to improve the admission process.

In the presented study, a structured admission and discharge management programme (VESPEERA) including follow-up care in general practices will be tested, thus providing a patient-centred and quality optimising enhancement of usual care.

The overall aim of this study is the development, implementation and evaluation of several transitional care components in general practitioners (GP) and hospitals.

### Objectives

Overall, the VESPEERA program is expected to reduce the number of avoidable rehospitalisations and emergency care contacts, to improve patient safety and patient involvement, to reduce overuse, underuse and misuse of health care, to improve the continuity of care and to improve interprofessional and cross-sectoral communication between patients, hospitals, GP-practices and the sickness fund “Allgemeine Ortskrankenkasse (AOK) Baden-Wurttemberg”.

## Methods/design

An open prospective quasi-experimental trial will be conducted in multiple centres. Development of study material has started in October 2017. Recruitment of patients and implementation of study components (intervention phase) has started in May 2018 and will last through September 2019, comprising a total of 17 months. Participants can be enrolled until September 2019. All evaluations and publications are planned to be completed by the end of September 2020. Figure 1 illustrates the study timeline.

**Fig. 1 Fig1:**
[figure not shown]
VESPEERA study timeline. Each study arm will receive different intervention components based on the point of study enrolment and the patient’s medical need, including structured assessment prior to admission and after discharge, automatically generated information for physicians and patients, a telephonic discharge conversation between hospital and general practice as well as a telephone monitoring for patients with a higher risk of rehospitalisation

### Study setting

The VESPEERA programme will be implemented in 25 hospital departments and 115 general practices in 9 predefined geographical areas in the federal state Baden-Wurttemberg in South-Germany. Hospitals sign a participation contract according to §140a SGB V. The intervention region can be expanded if hospitals from other districts are willing to participate. However, hospitals outside the intervention region are not actively invited to participate. A sample of 50 GP-practices within the same federal state but outside the intervention region will serve as control sites for the patient survey.

### Study population / eligibility criteria

GP-practices within the intervention region have to participate in GP-centred care (*Hausarztzentrierte Versorgung/* HzV). GP-centred care is a programme where, amongst others, the GP has a gate-keeping function (further description of the programme provided by Wensing et al. [13]. Furthermore, Gp-practices have to employ a Care Assistant in General Practice (*Versorgungsassistentin in der Hausarztpraxis/* VERAH). Inclusion criteria for patients are age of 18 years and older, ability to give consent, insurance with the sickness fund AOK Baden-Wurttemberg, participation in GP-centred care according to § 73b SGB V, and at least one hospitalization during the intervention phase. Patients residing in long-term care facilities are excluded from study participation.

### Intervention group

The VESPEERA programme comprises recommended practices regarding discharge and care management, which is reinforced by laws (§ 11 Abs. 4 SGB V, § 39 Abs. 1a SGB V, § 112 Abs. 2, Satz 5 SGB V). The planned intervention picks up these regulations for optimal care and offers suggestions for their implementation and enhancement. Patients will not be randomly assigned to a study arm, but receive different intervention components based on the point of study enrolment and the patient’s medical need (see Table 1 – adjusted SPIRIT figure).

**Table 1 Tab1:** Intervention components for all study arms

Interventions		*Study arm 1:*planned admission into a participating hospital	*Study arm 2:*planned admission into a non-participating hospital	*Study arm 3:*unplanned admission into a participating hospital	*Study arm 4:* unplanned admission into a non-participating hospital	*Study arm 5:* control group, not participating in VESPEERA
GP-practice	Interventions in the GP-practice before admission: (A) assessment for admission (B) admission letter and patient brochure	X	X			
Hospital	Interventions in the hospital: (C) telephonic discharge conversation (D) determination of HOSPITAL-Score and patient discharge information	X				
GP-practice	Interventions in the general practice after discharge: (E) assessment for planning of follow-up care (F) telephone monitoring, depending on the risk for rehospitalisation	X	X	X	X	

Assessment for Admission (A): Before a planned hospital admission, the VERAH collects patient information on basic data, admission diagnosis, medical history, existing prescriptions, medication plans and other medical information, social, living and legal situation, communication and care needs.

Admission letter and accompanying patient brochure (B): Based on the assessment for admission, an admission letter which also specifies how and when the practice is available by phone for the hospital staff is created. Patients receive a brochure that informs and prepares for the hospital stay.

Telephonic discharge conversation between GP-practices and hospital (C): For patients with complex interventions, medications or post-hospital care needs, a structured telephonic discharge conversation supports cross-sectoral exchange of information and clarification of responsibilities between the participating hospital and the responsible GP. In case of need, the AOK can be contacted to support the discharge process for example by providing medical products/ devices etc. in time.

Determination of HOSPITAL Score and patient discharge information (D): The participating hospitals collect data to determine the HOSPITAL Score, a score that indicates the risk for rehospitalisation within 30 days after discharge [14]. The score is communicated to the GP via the discharge letter. At the time of discharge, the patient receives patient discharge information, which summarizes the documents that the patient receives, follow-up care and appointments after discharge as well as different contact persons according to the respective care needs.

Assessment for planning of follow-up care (E): After hospital discharge, the patient has an appointment in the GP-practice (in case of need: home visit) with the VERAH. They conduct an assessment to determine the patients’ need for follow-up treatment and care. The GP receives a summary of the assessment, disclosing the patients’ care needs. Then, follow-up appointments, prescriptions and applications (such as rehabilitation or home care) can be determined and recorded. The patient receives a short summary of the arranged follow-up care plan. Based on the HOSPITAL Score, the GP determines the patients’ enrolment into the follow-up telephone monitoring. Patients with an intermediate or high risk for rehospitalisation, according to the HOSPITAL Score, should be enrolled in the follow-up telephone monitoring. For patients treated in a non-participating hospital, GP-practices have the option to gather data to determine the HOSPITAL Score. All data necessary to determine the score can be extracted from the discharge letter.

Post discharge telephone monitoring (F): If the HOSPITAL Score indicates an intermediate or high risk for rehospitalisation, the GP-practice coordinates and accompanies follow-up care through a structured telephone monitoring, which is limited to a time frame of 3 months after hospital discharge. The GP individually defines the content and frequency of the telephone monitoring, which is executed by the VERAH. The first phone call should be scheduled within the first 2 weeks after discharge. The last phone call should be scheduled 3 months after discharge. Any phone calls in between are defined in their interval by the GP.

### Control group

Using propensity score matching a control group from non-participating HzV-GP-practices in non-participating districts is built. Using claims-based data, age, gender, practice size and length of enrolment in GP-centred care and the district are considered to build the control group on practice level; to build a patient control group, age, gender, indication group and Charlson Comorbidity Index are used. Patients in the control group are not participating in the study and do not receive any intervention components.

The control group for the patient survey comprises patients that from approx. 50 comparable HzV-practices outside the intervention region. The inclusion criteria of the intervention group apply for patients of the control group.

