### Sample size calculation

Since large-scale implementation of the VESPEERA program in a geographical region was intended, the number of participating GPs and hospitals was not restricted. Based on the number of GP-practices who participate in HzV-Care and the number of GP-practices who participate in the PraCMan programme, a number of 115 GP-practices are expected to participate. An estimation of the patient sample size was made using claims-data and several assumptions for hospitalisation rates, rates for planned and unplanned admissions, rates of patients with a high risk of rehospitalisation as well as drop-out rates. Assumptions were made based on analyses of AOK claims-data. Admissions are expected to be planned and unplanned in 50% of the cases, respectively. 56% of planned admissions are made by a GP and therefore can be included in the VESPEERA programme. 40% of planned admissions are cases that are expected to be treated in a participating hospital department. After discharge, we calculated with a 20% drop-out rate for patients who are transferred into a nursing home, who pass away or who do not seek GP contact after discharge. 60% of discharged patients are expected to have a risk of rehospitalisation (HOSPITAL Score indicating an intermediate or high risk for rehospitalisation). Figure 2 gives an overview on the sample sizes in each study arm. Given the estimated sample size, we can estimate the effect size (based on the hospitalisation rates after the intervention) that can be detected. Based on claims-data different numbers of hospitalisations can be expected for each of the intervention groups. The alpha level is set to 5%. The following power considerations are based on chi square tests (to test for group differences) and adjusted for the hierarchical structure of the data. The implemented models in the primary analysis will most likely lead to even higher power values. However, we consider the hierarchical structure of the data with cases nested in patients nested in hospitals or practices, respectively. A relatively high ICC (0.3) can be expected when considering measurements within patients, however the number of cases per patient will be relatively small (approx. 1.6 cases per patient). The clustering by hospitals or practices is taken into account with an expected number of approx. 540 patients per hospital and a presumed ICC of 0.03, which is a realistic value in health services research [20]. Furthermore, we assume a rate of re-hospitalisations of 23% in the control group. With a power of 80%, the following reductions in each of the intervention groups can be shown: For study arm 1 a sample size of 1905 cases can be expected. Hereby, a reduction of approx. 8% (from 23% to approx. 15%) can be shown. The control group will be matched and, therefore, the sample size will be the same. For study arm 2 when compared to the control group, the same reduction is detectable, as the same number of cases can be expected as in study arm 1. In a last step, both the study arms 3 and 4 are compared to the control group using a level of significance of 2.5%. In study arm 3, we expect a sample size of 3266 and, thus, a reduction of approx. 7% (from 23 to 16%) can be shown. In study arm 4, a sample size of 4899 hospitalizations can be expected which allows to show a reduction of approx. 6% (from 23 to 17%).

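### The claims control group is not restricted to practices with a VERAH, and the long-term-care exclusion is not stated for it

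*Protocol article*

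**What the plan says.** **Entry to the intervention side** (Protocol article, Study population / eligibility criteria). Two rules apply to practices: "GP-practices within the intervention region have to participate in GP-centred care", and "Gp-practices have to employ a Care Assistant in General Practice". For patients, the section begins "Inclusion criteria for patients are age of 18 years and older, ability to give consent, insurance with the sickness fund AOK Baden-Wurttemberg" and goes on to require enrolment in GP-centred care and a hospital stay during the intervention phase. It then adds one exclusion: "Patients residing in long-term care facilities are excluded from study participation".

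**Claims controls** (Control group, first paragraph). The pool is defined thus: "a control group from non-participating HzV-GP-practices in non-participating districts is built". At practice level, "age, gender, practice size and length of enrolment in GP-centred care and the district are considered to build the control group on practice level". At patient level, "to build a patient control group, age, gender, indication group and Charlson Comorbidity Index are used".

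**Survey controls** (Control group, second paragraph). This paragraph describes about 50 comparable practices outside the region. It ends by carrying the intervention group's inclusion criteria over to control patients.

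**Primary model** (Primary analysis). A difference-in-difference logistic mixed model compares each arm with control. It adjusts for hospital service level and location, and leaves all other covariates to the matching.

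**The concern.** The study is not randomised, so the primary comparison depends on controls resembling the intervention side in everything except the programme. Two of the study's own entry rules do not appear in the definition of the claims controls.

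The VERAH rule matters because the Intervention group section gives the VERAH the pre-admission assessment (component A), the post-discharge assessment (E) and the execution of the telephone monitoring (F). Every intervention practice has such an assistant by rule; a control practice may have none. If rehospitalisation develops differently over time in the two kinds of practice, the interaction term takes up that difference together with the programme's effect.

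The long-term-care rule matters because residents may have a different rehospitalisation risk. If they are screened out of the intervention group only when patients enrol, the case mix changes on one side and in one period.

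**Working it through.** **Step 1: rules side by side.** No stated figure is at issue, so there is none to reproduce.

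| Rule | Intervention side | Claims controls | Primary model |
|---|---|---|---|
| Practice in HzV | required | required by the pool definition | not needed |
| AOK insurance | required | follows from the AOK claims source | not needed |
| Practice employs a VERAH | required | not required, not matched | not adjusted |
| Patient not in long-term care | required | not stated, not matched | not adjusted |

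The first two rules carry over; the last two do not.

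**Step 2: what the estimator removes.** On the risk scale, write D = (I1 − I0) − (C1 − C0), where I and C are the rehospitalisation rates on the intervention and control sides and 0 and 1 mean before and after. A negative shift in D favours the programme. The model is logistic, so cancellation on this scale holds only approximately there.

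**Step 3: VERAH.** Let s be the share of control cases from practices without a VERAH. Let d be the before-to-after change in such practices minus that in practices with one, absent the programme. Then D = effect − s × d.
- A stable difference means d = 0 and no bias.
- The article gives neither s nor d. Purely as an assumption, s = 0.5 and d of 1 to 2 points in either direction give 0.5 × 1 = 0.5 to 0.5 × 2 = 1 point, in either direction.
- The eligibility section does not say since when the VERAH must have been employed. If a practice hires one in order to qualify, the assistant's own effect falls into I1 − I0.

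**Step 4: long-term care.** Let q be the share of residents and r their rehospitalisation rate, with 23% for everyone else. The 23% is the control rate assumed in Sample size calculation; q = 5% to 15% and r = 15% to 38% are assumptions for illustration.
- *Residents among controls in both periods, none on the intervention side.* The control level shifts by q × (r − 0.23), from 0.15 × (0.15 − 0.23) = −1.2 points to 0.15 × (0.38 − 0.23) = +2.25 points. The shift is the same before and after, so D is unchanged.
- *As above, but the control share of residents rises by 3 points.* C1 − C0 shifts by 0.03 × (0.15 − 0.23) = −0.24 to 0.03 × (0.38 − 0.23) = +0.45 points. D shifts by the same amounts with opposite sign.
- *Residents in the intervention side's before cases but screened out afterwards.* I1 − I0 shifts by −q × (r − 0.23), which ranges from −2.25 to +1.2 points. If controls keep a stable share of residents, all of this enters D. If residents are removed from controls only, C1 − C0 is still unaffected and the bias stays. A filter on controls alone therefore does not cure this case.
- *Same patients observed before and after.* If non-residents at enrolment were also non-residents earlier, this reduces to the first case.

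Neither Primary analysis nor Data collection and management says which patients supply the before cases, so the article does not settle which case applies.

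**The case against.** The strongest reply is that this is a condensed article and that extraction rules for a claims cohort usually stand in the full protocol or analysis plan. That would dispose of the point if the article were merely silent. It is not: it names a pool, lists the matching variables at two levels, and says that covariates outside the model are dealt with by the matching. Followed as written, it leaves both differences in place.

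A second reply is that the last sentence of the Control group section applies the inclusion criteria to control patients. Part of this stands. The sentence is ambiguous in reach and could be read as covering all controls. But it stands in the survey paragraph, speaks of inclusion criteria while long-term care is an exclusion, and cannot supply a rule about practices. The long-term-care half is therefore the weaker one. A reader might infer that residents are admitted to the control pool; the article shows only that their exclusion is not stated.

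Third, difference-in-difference cancels stable differences, and the planned interrupted time-series analysis compares trends before and after. The first part stands and limits the concern to trends and case mix. The time-series analysis is secondary. It can reveal diverging trends but does not change the control group used for the primary result.

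Two stronger readings should be resisted:
- A reader might infer from "a 20% drop-out rate for patients who are transferred into a nursing home, who pass away or who do not seek GP contact" that such patients are removed from the intervention arms but not from controls. That figure is a planning allowance in Sample size calculation. The Analysis sets section keeps assigned patients in their arm by intention to treat.
- A reader might infer that participating practices come mainly from the PraCMan case-management programme and so differ from controls on that too. The article says only that the expected 115 practices were derived from the numbers in HzV and in PraCMan, and that all eligible practices in the districts are contacted.

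**Conclusion.** The point holds in a limited form. The VERAH half is firm: an entry condition for intervention practices, tied to the staff who deliver three components, is neither a condition nor a matching variable for control practices, and the model does not adjust for it. The long-term-care half is a gap in the definition of the claims controls, not proof that residents are included.

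It would be too broad to say that controls escape the entry criteria altogether, since HzV participation and AOK insurance do apply to them.

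Size and direction cannot be derived from the documents. The illustrations above rest on assumed shares, rates and trends, run in both directions and should not be added together. A reader might wish to express them as a fraction of the 8-point reduction for arms 1 and 2. The article does not support this: the 8 points are a detectable difference, not a claimed effect, and every input to the bias is assumed.

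**What to change.** In the Control group section:

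1. Restrict the pool of control practices to HzV practices that employ a VERAH. If the pool becomes too small, match on VERAH employment instead.
2. Exclude patients resident in long-term care at the index stay from both the intervention and the control cohort, in both the before and the after period.

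If both rules were always meant to cover the claims controls, a short statement there settles the matter, provided the residence rule names both cohorts and both periods.

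The cost is a somewhat smaller control pool. The change also assumes that VERAH employment and residence status can be obtained for the control districts, which the article does not show; this should be confirmed with the sickness fund and the contract organisation before the controls are drawn.
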